### Data management

Trial-relevant data will be documented in the case report form (CRF). The original CRFs will remain at the investigating centre and copies will be sent to the primary investigating centre, i.e. University Heidelberg. Data extraction and analysis will be made by the contract research organization, R&P Ryschlick and Partner GmBH (Burscheid, Germany). Data will be analyzed for completeness, validity and plausibility. The investigator will be consulted in case of uncertainty of the data.

### Safety evaluation and reporting of adverse events

Patients will receive regular medical treatment, including any necessary emergency treatment, throughout the duration of the trial. Serious adverse events (SAE) are defined as the need for re-operation, prolonged hospitalization, life-threatening situations, readmission for any reason, and death. The principal investigator must be informed about all occurring SAEs within 24 hours of knowledge of the event. All SAEs must be reported to the principle investigator.

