### Secondary endpoints

Long-term EWL at 60 months after surgery, morbidity, mortality, course of obesity-related co-morbidities (T2DM, hypertension, joint pain, sleep apnoea, dyslipidemia), vitamin status, incidence and/or course of GERD and QoL (as defined by the SF 36) and dumping syndrome (as defined by the Sigstad score) will form the secondary endpoints. The course of obesity-related co-morbidities is assessed by laboratory examinations and current medication use. T2DM remission will be measured by HbA1c, fasting glucose and medication use. Hypertension will be monitored by medication and blood pressure measurements. The course of joint pain and dyslipidemia are assessed by pain and respectively lipid metabolism medication. The course of sleep apnoea is analysed by patients’ application of CPAP-mask. Nutritional substitution will be assessed using a questionnaire which was developed in the bariatric centre of the University of Heidelberg. GERD incidence and course of GERD will be assessed with EGD and by using GSRS and GIQLI as standardized questionnaires. To evaluate QoL, the validated SF-36 questionnaire will be used. The Dumping score will be evaluated by using the validated Sigstad score. Secondary endpoints will be evaluated preoperatively, at discharge, 3-6, 12, 24, 36, 48 and 60 months postoperatively. Questionnaires will be filled out 12, 24 and 60 months after surgery. The EGD will be performed 12 and 60 months postoperatively.

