### Safety measures

Safety analysis includes frequency of SAEs and complications. Homogeneity of the study arms will be described by comparing demographic data with baseline values.

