### Withdrawals and stopping guidelines

Patient withdrawal from the trial is possible at any time and without explanation. The trial will be ended in cases of insufficient patient recruitment and a high rate of SAEs due to SG or RYGB.

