### Data safety monitoring board

Reports of SAEs will be collected by an independent data and safety monitoring board (DSMB). Furthermore, the DSMB will inform the trial management about relevant imbalances between the two groups.

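### The SAE definition counts every readmission whatever its cause, so elective admissions without harm enter the descriptive safety comparison of the two arms

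*Protocol article*

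**What the plan says.** All of the relevant text is in the protocol article.

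- *Safety evaluation and reporting of adverse events* gives the definition: "Serious adverse events (SAE) are defined as the need for re-operation, prolonged hospitalization, life-threatening situations, readmission for any reason, and death". It adds a reporting duty: "The principal investigator must be informed about all occurring SAEs within 24 hours of knowledge of the event". It gives no start or end of SAE collection, no exemption for elective admissions, and no step that assesses cause.
- *Safety measures* names the output: "Safety analysis includes frequency of SAEs and complications".
- *Data safety monitoring board* has the board collect the SAE reports, and "the DSMB will inform the trial management about relevant imbalances between the two groups".
- *Withdrawals and stopping guidelines* is the only place where attribution appears: "The trial will be ended in cases of insufficient patient recruitment and a high rate of SAEs due to SG or RYGB".
- *Secondary endpoints* sets the length of follow-up: "Secondary endpoints will be evaluated preoperatively, at discharge, 3-6, 12, 24, 36, 48 and 60 months postoperatively".

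**The concern.** A readmission counts as an SAE here regardless of why it happened. Take three patients followed for some years after surgery. One is admitted for planned skin reduction after a good result, one for an uncomplicated delivery, and one for a staple-line leak. Under the printed rule each has one SAE, although only the third has been harmed.

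The consequence lies in the comparison between arms. Events that are not harm, added at the same rate to both arms, pull the ratio of SAE proportions towards 1 and make a real safety difference harder to see. If they occur at different rates, they produce a difference that has nothing to do with safety. Safety is part of the reason for comparing these two procedures, and the board is asked to watch for imbalance, so the tabulated SAE count should measure what its name says.

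**Working it through.** **Does any other section narrow the definition?** No. *Safety measures* and *Data safety monitoring board* use SAEs without a filter for cause. The stopping guideline adds attribution to the procedure, but only for the decision to end the trial.

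**Illustration of size.** The article calculates no SAE figure, so there is none to reproduce. Inputs:

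- Harm risk h: 5.9 % (SG) and 10.3 % (RYGB), the overall complication rates cited under *Ethical considerations*. No time frame is given for them. Ratio 10.3 / 5.9 = 1.75; difference 4.4 points.
- Elective, non-adverse admission risk q: **assumed**, because the article gives none. Range 5 to 30 %, equal in both arms and independent of harm.
- Arm size: 124 (*Sample size*).

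The proportion with at least one SAE as defined is 1 − (1 − h)(1 − q). The share of those patients who have only an elective admission is (1 − h)q divided by that proportion.

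| q (assumed) | SG | RYGB | Ratio | Difference (points) | Elective only, SG / RYGB |
|---|---|---|---|---|---|
| 0 % | 5.9 % | 10.3 % | 1.75 | 4.4 | 0 / 0 % |
| 5 % | 10.6 % | 14.8 % | 1.39 | 4.2 | 44 / 30 % |
| 10 % | 15.3 % | 19.3 % | 1.26 | 4.0 | 61 / 47 % |
| 20 % | 24.7 % | 28.2 % | 1.14 | 3.5 | 76 / 64 % |
| 30 % | 34.1 % | 37.2 % | 1.09 | 3.1 | 83 / 72 % |

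Worked line for q = 10 %: SG 1 − 0.941 × 0.90 = 0.153; RYGB 1 − 0.897 × 0.90 = 0.193. With 124 patients per arm that is about 19 versus 24 patients with an SAE, against about 7 versus 13 (124 × 0.059 and 124 × 0.103) when only harm is counted.

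The ratio falls quickly. The absolute difference shrinks only by the factor (1 − q), for example 4.4 × 0.90 = 4.0.

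**If elective admissions differ between arms.** Set harm equal at 8.1 %, the midpoint of the two cited rates, and assume elective admissions of 10 % and 20 %. The SAE proportions become 1 − 0.919 × 0.90 = 17.3 % and 1 − 0.919 × 0.80 = 26.5 %, a gap of 9.2 points with no difference in harm. With 5 % and 10 % the gap is 4.6 points (12.7 % versus 17.3 %). Both pairs are assumptions; nothing in the article shows that an imbalance exists or in which direction it would run.

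**Sensitivity to the harm rate.** *Risk-benefit ratio* gives SG morbidity of up to 17.5 %. With that value and q = 10 %, the elective-only share in SG is 0.825 × 0.10 / (1 − 0.825 × 0.90) = 0.0825 / 0.2575 = 32 %, not 61 %. The illustration depends heavily on its inputs.

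**The case against.** The strongest reply is that the sentence defines serious *adverse* events. On that reading an event must first be adverse, and the wording on readmission only removes a judgement about relatedness. This is a possible reading, but the printed text does not say it, and the phrase used points the other way. Seven centres could apply it differently.

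Second, wide capture is a sound choice for rapid reporting. It keeps discretion away from the person who reports, and the stopping guideline can attribute cause later. This stands, and it is why the fix leaves reporting alone. It does not justify using the unfiltered count as the comparison between arms.

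Third, the assessment of harm does not rest on SAE counts alone. Morbidity, mortality and re-operation rate are secondary endpoints, and complications are tabulated beside SAEs. The board receives reports, which can show the reason for admission, and it is asked about relevant imbalances, which leaves room for judgement. This also stands and limits the consequence.

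A reader might go further and infer that better weight loss will be scored as harm, that a false signal is likely, or that the trial could be stopped on elective admissions. The article does not support this. It gives no elective-admission rate and no evidence of an imbalance. It specifies a frequency, not a significance test, for SAEs. Its stopping wording requires attribution to a procedure.

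**Conclusion.** The point holds as a flaw in the definition of a descriptive safety measure. The text makes every readmission an SAE, and two other sections use those SAEs to compare the arms, so elective admissions without harm would be counted. The rule is stated in the article; it is not a detail left to a fuller document.

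The size cannot be determined. The table shows what would happen under assumed elective-admission risks that are equal and independent of harm, with complication rates that carry no stated time frame. That SAE collection runs to 60 months is inferred from the visit schedule; a shorter window would mean fewer such admissions. The primary excess-weight-loss analysis and the sample size are untouched, and the effect on stopping is limited by the attribution wording. The matter ranks as a cheap improvement.

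**What to change.** Leave the reporting duty as it is: every readmission is still reported. Then:

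1. Record the reason for each readmission, and have it classified, without knowledge of the arm, as due to an untoward medical event or not. A scheduled admission to treat a complication stays an SAE. A simple planned/unplanned split would be the wrong filter, because it would drop scheduled treatment of real harm such as sleeve stenosis, which the article lists as a complication.
2. In *Safety measures*, base the SAE comparison on the number of patients per arm with at least one SAE involving an untoward event. List all-cause readmissions and non-adverse elective admissions on separate lines.
3. Give the monitoring board the same breakdown.

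The cost is one case report form field, a blinded classification and one extra table. No information is lost, because the all-cause line remains.

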### Study visits

Study documentation and visits of patients will be performed by both surgeons and study nurses. Since the trial is designed as observer and patient blind RCT, information about the surgical procedure will not be reported during the follow-up examinations. There will be 9 study visits during the BariSurg RCT (see Fig. 1). During the first postoperative year, study visits will be performed at discharge, 3–6 months and 12 months postoperatively. Then visits will be performed annually. Every postoperative study visit includes data collection of weight, morbidity, mortality, course of obesity-related co-morbidities (including laboratory parameters and current medication), analysis of nutritional supplementation, occurrence of GERD and analysis of dumping syndrome using the Sigstad score. In addition to the above mentioned information, extended study visits will yearly assess general laboratory parameters, EGD results and the questionnaires (SF-36, GIQLI, GSRS, see Fig. 1).

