### Risk-benefit ratio

SG is associated with a morbidity rate between 0–17.5 % and a mortality rate between 0–1.2 % [13]. The most frequently occurring postoperative complications are insufficiencies/fistulas at the staple line, leakage, stenosis of the sleeve and dilatation of the sleeve [5]. RYGB has a morbidity rate of 2-10 % and a mortality of 0.5-0.8 % [7, 12, 15]. Frequently observed complications include anastomotic insufficiency, especially with regard to the gastrojejunostomy, and dumping syndrome. Dumping syndrome is observed in 42 % after RYGB and up to 29 % after SG [31–33]. Therefore patients will be assessed for dumping syndrome. If the diagnosis dumping syndrome is confirmed patients will get the optimal treatment for dumping syndrome [28]. For both bariatric procedures, nutritional supplementation might be necessary for the remainder of the patient’s life.

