### Good clinical practice

The BariSurg trial will be conducted according to national and international trial standards (ICH-GCP, Declaration of Helsinki 2008).

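### The closed SAE definition omits lasting disability and other medically important events, so a harm with none of the listed features has no stated 24-hour report or route to the DSMB

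*Protocol article*

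**What the plan says.** The section on safety evaluation and adverse-event reporting gives the definition in one sentence: "Serious adverse events (SAE) are defined as the need for re-operation, prolonged hospitalization, life-threatening situations, readmission for any reason, and death". The same section sets the expedited route: "The principal investigator must be informed about all occurring SAEs within 24 hours of knowledge of the event".

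The section on the data safety monitoring board says "Reports of SAEs will be collected by an independent data and safety monitoring board (DSMB"), and adds that "the DSMB will inform the trial management about relevant imbalances between the two groups". The section on withdrawals and stopping names two grounds for ending the trial: poor recruitment and a high SAE rate attributable to either operation. The second is the only safety ground.

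Harm is also recorded outside the SAE route. Under Study visits: "Every postoperative study visit includes data collection of weight, morbidity, mortality, course of obesity-related co-morbidities". The same sentence adds nutritional supplementation, reflux and dumping. The secondary endpoints include morbidity, mortality and vitamin status. Under Safety measures: "Safety analysis includes frequency of SAEs and complications".

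**The concern.** The definition is worded as complete. Nothing in it marks the five items as examples. Three of the five (repeat surgery, a longer stay, readmission) are identified by the use of surgery or hospital care, and the other two are threat to life and death. Lasting disability is not among them, and there is no general item for an event that is medically important for some other reason.

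This matters because the trial follows patients for five years after operations with recognised late effects. The article provides for vitamin deficiency during follow-up, says of both procedures that "nutritional supplementation might be necessary for the remainder of the" patient's life, and lists stenosis and dilatation among the complications of the sleeve. If one of these left a lasting deficit that was handled without readmission, repeat surgery or threat to life, it would count as no SAE. A readmission for an unrelated cause would count as one. The trial compares two operations whose balance of benefit and risk is the open question, so the events that reach safety oversight quickly should be chosen by seriousness, not mainly by where they were treated.

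**Working it through.** No formula applies, and the article gives no figure to reproduce on this point. The check sets the definition beside the provisions that depend on it.

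**Step 1: which harms the definition captures.**

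| Harm | Listed feature met | SAE as written? |
|---|---|---|
| Threat to life, treated without admission | threat to life (not tied to hospital care) | yes |
| Lasting disability leading to readmission, longer stay or repeat surgery | one of those three | yes |
| Lasting disability with none of the five features | none | no |
| Other medically important event with none of the five features | none | no |

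The gap is the last two rows.

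**Step 2: what depends on the label.**

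- 24-hour notice to the principal investigator: stated for SAEs only.
- Data the DSMB is said to collect: SAE reports only. Its further task on imbalances between groups is not limited to SAEs, but the article names no other data that it receives.
- Safety ground for ending the trial: the SAE rate only.

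A harm in the last two rows therefore has no stated expedited report, no stated route to the DSMB and no weight in the safety ground for ending the trial.

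**Step 3: what still captures it.** Morbidity is collected at every postoperative visit, vitamin status is a secondary endpoint, and complications are counted in the safety analysis beside SAEs. The harm can enter the database and the final comparison.

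**Step 4: the difference in timing.** Postoperative visits are at discharge, 3–6, 12, 24, 36, 48 and 60 months. From month 12 the interval is 24 − 12 = 12 months, and it stays at 12 months to month 60. An event noticed only at a scheduled visit may thus be recorded up to 12 months after onset. An SAE is to be reported within 24 hours of becoming known. The two clocks start at different points (onset and knowledge), so this shows the kind of delay possible and is not a measured one.

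**The case against.** The strongest reply is that this is a condensed article. Adverse-event criteria, the SAE form and the DSMB's working rules are commonly left to the full protocol, and no other section contradicts the definition. That is a fair answer to silence, and it covers which further data the DSMB receives. It does not cover the definition itself, which the article states in full and words as exhaustive.

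The second reply is that safety does not rest on the SAE count alone. Morbidity, laboratory values, supplementation, vitamin status and complications are all collected, and complications are analysed. This stands, and it limits the point to expedited reporting and oversight.

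Four stronger readings are tempting but not supported:

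- A reader might infer that serious harm managed outside hospital can never be an SAE. A threat to life counts wherever it is treated, and disability that leads to one of the other listed events counts too.
- A reader might infer that these harms cannot reach the DSMB. The article does not say so. The board's task on imbalances is not confined to SAEs, and the article neither states nor excludes that morbidity data go to it.
- A reader might infer a breach of the standard that the article adopts: "The BariSurg trial will be conducted according to national and international trial standards (ICH-GCP", among others. The text of that standard is not in the documents, so conformity cannot be tested here.
- A reader might wish to put a number on the missed events or set it against expected deaths. The documents give no rate for lasting harm without a listed feature, so neither can be done. Nor does the article say that it expects permanent injury from vitamin deficiency or stenosis; the example under the concern is an illustration.

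**Conclusion.** The point holds in a limited form. As written, the SAE definition leaves out persistent or significant disability or incapacity, and other medically important events. A lasting harm with none of the five listed features has no stated 24-hour report, no stated route to the DSMB and no weight in the SAE-based ground for ending the trial, although it may be recorded and analysed as morbidity or a complication.

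The number of patients affected cannot be given from the documents. The class is narrow, and the primary endpoint is untouched. The change is still worth making, because one sentence controls three safeguards and is simple to amend. The conclusion assumes that the article's definition is the one in force. If the full protocol has a wider list, the article misreports it and the two need to be aligned.

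**What to change.** Add two items to the SAE definition: *persistent or significant disability or incapacity*, and *other medically important event requiring intervention to prevent one of the listed outcomes*. State that both follow the same 24-hour report and the same route to the DSMB. First check the full protocol and the SAE form, so that all three carry one list.

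This changes a reporting definition only, not patient care. It costs a line in the protocol and on the form, a note to the centres and a few more SAE reports. Recruitment has already begun, so the amendment should state the date from which the wider definition applies. Complications already recorded can be screened against it, so that the SAE comparison uses one definition throughout.

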### Unblinding

Blinding of patients has been done many times even in surgery [34–36]. Besides randomization, blinding of patients (and observers) reduces bias. Subsequently, internal and external validity will be increased. The fact that this study will be a patient and observer blinded study made a thoroughly ethical and clinical evaluation necessary. Based on the given evidence there is reliable data available that both procedures are similar in their clinical efficacy regarding excess weight loss, diabetes remission and complication rates [13–15]. Taking aside historical considerations and looking only at the RCT regarding RYGB and SG one can truly suggest to patients that both procedures are equally effective and safe.

During the BariSurg trial, all patients get extensive oral and written information about both procedures with all relevant pros and cons. Patients are informed that they will not know which procedure will be performed. Randomization will be performed intraoperatively after confirming that both procedures can be performed safely. All relevant documents including operation report and discharge letter state that the patient was enrolled in a randomized controlled patient and observer blind clinical trial comparing RYGB and SG and that the patient does not know about the procedure. These documents also include an emergency number which patients or physicians can call any time (24 hours, 365 days service) in case unblinding is necessary. Thus, blinding patients during the BariSurg trial is reasonable both from a clinical point of view as well as from ethical considerations.

### Statistical methods

#### Sample size

According to a systematic review by Fischer et al. the mean EWL two years after SG and RYGB was 56.1 % and 68.3 % respectively, with a common standard deviation of 22.5 % [13]. Based on these results, the null hypothesis is that there exits inferiority of SG compared to RYGB in EWL 24 months after surgery. Based on the assumption that a difference in EWL of 10 % or more is clinically relevant, the margin to consider EWL as similar is set to 9 %. The power calculation for a non-inferiority trial with a one-sided t-test (alpha = 0.025 % and beta = 20 %) and a standard deviation of 22.5 % revealed that 99 patients per intervention group need to be randomized. Since a high dropout rate of 20 % is expected, a further 25 patients per intervention group should be randomized. Hence a total of 124 patients for each group will be recruited (overall 248 patients).

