### Primary endpoint

The primary endpoint is defined as EWL at 24 months after surgery (RYGB or SG). Power calculation was made according to the systematic review of Fischer et al. [13].

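### The 80 % power holds only for an unstated true difference of 0, while the review means quoted as planning data lie 12.2 points apart, beyond the 9-point margin

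*Protocol article*

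**What the plan says.** Three places in the protocol article bear on this.

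- **Primary endpoint:** "Power calculation was made according to the systematic review". It does not say which of the review's figures were used.
- **Statistical methods, Sample size:** from the same review, "the mean EWL two years after SG and RYGB was 56.1 % and 68.3 % respectively", "with a common standard deviation of 22.5" %. The next sentence derives the null hypothesis of inferiority from these results. The paragraph then takes the view that "a difference in EWL of 10 % or more is clinically relevant", and "the margin to consider EWL as similar is set to 9" %. The calculation uses a "one-sided t-test (alpha = 0.025 % and beta = 20" %) and the 22.5 % standard deviation. It arrives at 99 per arm, raised to 124 per arm (248 in total) for 20 % dropout. No true difference under the alternative is given. Analysis of primary endpoint puts any RYGB minus SG difference of delta or more in H0.
- **Unblinding:** one sentence cites the review (reference 13) together with two further references (14, 15) as reliable evidence that the procedures are similar in excess weight loss (EWL). The next sentence, expressly limited to the randomized trials, says "one can truly suggest to patients that both procedures are equally effective and safe".

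**The concern.** A reader of the Primary endpoint and Sample size sections will take the 80 % as resting on the review. The review's means differ by more than the margin, and by more than the 10 points the plan calls clinically relevant. Power for a non-inferiority test depends on the distance between the margin and the assumed true difference, so the assumed difference is as important an input as the margin or the standard deviation. It is the one input not printed, and the only visible candidate for it, the pair of quoted means, gives a completely different answer.

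What is at stake is how the power for the primary hypothesis is understood, both now and when a result has to be interpreted. Type I error is not affected: if SG really were 12.2 points worse, a test that fails to declare non-inferiority would be working correctly.

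**Working it through.** **Inputs (Sample size paragraph).** SD 22.5; margin 9; means 56.1 (SG) and 68.3 (RYGB); power 80 %; 99 per arm before dropout. All EWL figures are read as percentage points. Alpha is printed as 0.025 % and is taken here as 0.025 one-sided.

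**1. Reproduce the plan's figure.** With true difference d,

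n per arm = 2 (z₀.₉₇₅ + z₀.₈₀)² SD² / (9 − d)².

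At d = 0: 2 × (1.96 + 0.8416)² × 22.5² / 9² = 98.1, so 99. The noncentral t distribution gives 79.97 % power at 99 per arm. Dropout: 99 / 0.80 = 123.75, so 124 per arm. Every stated number is reproduced.

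**2. Try other readings.**

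- d = 1, 2 or 3 points: 125, 163 or 221 per arm.
- Margin 10 with d = 0: 80 per arm.
- One-sided alpha 0.05: 78 per arm.
- Alpha taken literally as 0.025 % (0.00025): 234 per arm.
- Two-sided superiority test on 12.2 points: 54 per arm.

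Of the readings tried, only d = 0 with alpha 0.025 gives 99.

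**3. Place the quoted means.** 68.3 − 56.1 = 12.2. This is above 9 (the margin) and above 10 (the clinically relevant difference), so it lies in H0.

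**4. Chance of declaring non-inferiority by true deficit.** The noncentrality parameter is (9 − d) / SE, with SE = 22.5 × √(2/n). This is 3.20 at 99 per arm and 2.86 at 124 per arm.

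| True RYGB − SG (points) | 99 evaluable per arm | 124 evaluable per arm |
|---|---|---|
| 0 | 80.0 % | 88.0 % |
| 1 | 70.2 % | 79.6 % |
| 2 | 58.6 % | 68.4 % |
| 3 | 46.3 % | 55.2 % |
| 6 | 15.2 % | 18.0 % |
| 9 | 2.5 % | 2.5 % |
| 12.2 | 0.16 % | 0.10 % |

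At 12.2 points and 99 per arm, the normal approximation gives 0.15 % and simulation 0.16 %. No sample size gives 80 % power there, because 12.2 exceeds the margin.

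**5. The same result on the observed scale.** At the planning SD and 99 per arm, non-inferiority is declared only if the observed deficit is below 9 − 1.972 × 3.20 = 2.69 points.

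**The case against.** The strongest reply is that zero is the usual design alternative in a non-inferiority trial and that the article gives reasons for it elsewhere. The Background reports randomized trials with comparable EWL, and the Unblinding section says much the same. The calculation sentence itself takes only the standard deviation as a numerical input from the review, and the means can be read as motivating why inferiority was placed in H0. All of this stands. It shows that zero can be defended, but the Sample size paragraph neither states it nor draws on those trials. It prints contrary means instead, and the Primary endpoint section credits the review without limiting that credit to the SD. The Background's description of the review's difference as not significant is not evidence that the difference is zero.

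A reader might go further and infer that H0 is true and that a failed trial is the expected result. The documents do not support that. They give no confidence interval for the 12.2 points. The Discussion also describes a systematic review with the same 24-month finding, under a different reference number, as showing poor data quality in the SG literature. The 0.16 % is therefore what the quoted means would imply if true, and it is one end of a sensitivity range.

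A reader might also set the Unblinding statement about equal effectiveness directly against the 12.2 points. That sentence is limited to the randomized trials, so it does not contradict the review means. The tension is with the sentence before it, which cites the review itself for similar EWL.

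Finally, rules for reporting and reading confidence intervals may be in an analysis plan that is not shown, so their absence here is not part of this point.

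**Conclusion.** The point holds as a fault in the power statement. The arithmetic of 99, 124 and 248 is correct for a true difference of 0. That condition is unstated, and the statement is attributed to a review whose quoted means differ by 12.2 points, 3.2 beyond the margin.

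Under those means, power would be about 0.16 % instead of 80 %. The practical sensitivity matters more: a true deficit of 3 points, one third of the margin, leaves 46 %.

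These figures assume a common SD of 22.5, normally distributed outcomes, equal arms with 99 evaluable each, and one-sided alpha 0.025. That zero was used is inferred from the arithmetic. The printed alpha of 0.025 % is a separate slip, and correcting it does not remove this problem.

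**What to change.** 1. In the Sample size paragraph, state that 80 % power with 99 evaluable per arm is conditional on a true difference of 0, at one-sided alpha 0.025.
2. Justify the zero separately from the review means, for example by the randomized trials that the Background and Unblinding sections cite for comparable EWL.
3. In both the Primary endpoint and Sample size sections, attribute only the SD to the review, and acknowledge that its 12.2-point difference exceeds the margin.
4. Give power at a few non-zero deficits, for example 3, 6 and 12.2 points (46 %, 15 % and 0.16 % at 99 per arm).
5. In the Unblinding section, reconcile the sentence that cites the review for similar EWL with the 12.2-point difference quoted under Sample size.

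The cost is wording and a less favourable power statement. Sample size, margin and test need no change.

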### Sample size

A total of 248 patients will be randomized, with 124 patients assigned to each treatment arm. A dropout rate of approximately 20 % is considered realistic and has been accounted for the total number of randomized patients.

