### Analysis of primary endpoint

The primary endpoint is percent of EWL 24 months after surgery. To formalize the statistical approach, the following notations will be used: μRYGB/μSG, population mean of primary endpoint in RYGB/SG group. The following one-sided non-inferiority test problem is defined asH0: μRYGB - μSG > = delta vs.H1: μRYGB - μSG < delta

(For definition and specification of delta, see sample size calculation). This hypothesis will be tested using a one-sided t-test applied to each protocol population (see below). A low number of missing values for the primary endpoint is expected. If any values are missing, they will be replaced by methods of multiple imputation.

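### The one-sided significance level of the primary test is misprinted as 0.025 % where the stated 99 patients per arm imply 2.5 %

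*Protocol article*

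**What the plan says.** The Sample size section under Statistical methods specifies a "one-sided t-test (alpha = 0.025 % and beta = 20" per cent. In the same passage "the margin to consider EWL as similar is set to 9" per cent, and the calculation, using "a standard deviation of 22.5 % revealed that 99 patients per intervention group need to be randomized". A 20 % dropout allowance then adds 25 per group. The result is 124 per group and 248 overall, which agrees with the shorter Sample size section under Methods/Design ("with 124 patients assigned to each treatment arm").

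Analysis of primary endpoint sets out the hypotheses, refers back to the sample size calculation for delta, and states: "This hypothesis will be tested using a one-sided t-test". It gives no significance level and no confidence-interval rule. No other section of the article gives a level for this test.

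**The concern.** An alpha of 0.025 % is 0.00025, one hundred times smaller than 0.025. Beta in the same bracket is correctly expressed in per cent, so nothing in the sentence itself tells the reader that alpha is on a different scale. The figure matters because it is the decision threshold of the confirmatory test and appears only once. As printed, the threshold and the number of patients cannot both be right. A reader can recover the intended level only by redoing the calculation with a true difference that the article does not state.

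**Working it through.** **Inputs** (Statistical methods, Sample size, unless noted)
- SD = 22.5 and margin = 9 percentage points of EWL
- One-sided test, beta = 20 %, so z for power = 0.8416
- Allocation 1:1 (124 per arm, both Sample size sections)
- True difference: not stated, taken as 0. The cited review means ("the mean EWL two years after SG and RYGB was 56.1 % and 68.3 % respectively") differ by 68.3 − 56.1 = 12.2 points. That exceeds the margin, so they cannot be the planning difference.

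**Formula** (normal approximation)

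n per arm = 2 × (z for alpha + z for power)² × SD² / margin²

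Here 2 × SD² / margin² = 2 × 506.25 / 81 = 12.5.

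**Step 1: reproduce the plan's figure with alpha = 0.025**
- z = 1.960, so n = 12.5 × (1.960 + 0.8416)² = 98.1, rounded up to 99.
- Power at 99 per arm is 80.4 % (normal) or 79.97 % (noncentral t). The exact t-test reaches 80 % at 100 per arm, an immaterial difference.
- Dropout: 99 / 0.8 = 123.75, rounded up to 124 per arm, 248 in total. All stated figures are reproduced.

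**Step 2: use alpha as printed, 0.00025**
- z = 3.481, so n = 12.5 × (3.481 + 0.8416)² ≈ 233.5, rounded up to 234. The exact t-test gives 237.
- With 20 % dropout: 237 / 0.8 = 296.25, so 297 per arm against 124 planned.
- Standard error at 99 per arm: 22.5 × √(2/99) = 3.198. Power = Φ(9/3.198 − 3.481) = Φ(−0.667) = 25.3 %, or 23.9 % by noncentral t.
- Even if all 124 per arm were evaluable, power would be 37.0 % (normal) or 35.6 % (t).

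**Step 3: can another level explain 99?**

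| One-sided alpha | n per arm (normal) | n per arm (exact t) |
|---|---|---|
| 0.00025 | 234 | 237 |
| 0.0025 | 167 | 169 |
| 0.0125 | 119 | 121 |
| 0.025 | 99 | 100 |
| 0.05 | 78 | 78 |

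Solving for alpha at 99 per arm and 80 % power gives 0.0243 (normal) to 0.0251 (t).

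**Step 4: does this depend on the assumed difference of 0?** For 99 per arm to give 80 % power at 0.00025, the margin plus SG's true advantage would have to be (3.481 + 0.8416) × 3.198 = 13.8 points. SG would have to be truly better by 13.8 − 9 = 4.8 points. Nothing in the article suggests such a premise, and the cited review means point the other way.

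**Step 5: effect on the decision boundary** (99 per arm, observed SD 22.5)
- At 0.025: 9 − 1.972 × 3.198 = 2.7. SG may be observed up to 2.7 points worse and still be declared non-inferior.
- At 0.00025: 9 − 3.540 × 3.198 = −2.3. SG would have to be observed at least 2.3 points better.

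**The case against.** The strongest reply is that this is an evident typographical slip. The margin, SD, power and group size together identify 2.5 %, and almost every quantity in that paragraph carries a per cent sign, so a stray one is easy to understand. An article also need not repeat alpha in each section, and Secondary analyses refers to an analysis plan, not shown here, that may state the level correctly. All of this stands as an account of the cause. It does not make the printed value right. The article states the level rather than leaving it to another document, states it wrongly, and corrects it nowhere.

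A reader might infer more than the document supports:
- *That the trial is underpowered.* It is not. The low power arises only if 0.00025 is applied literally, and the planned numbers deliver 80 % at 2.5 %.
- *That 0.025 % was intended, or that the threshold was left open to be chosen after the data.* Nothing indicates either. A literal reading would make the test stricter, so it could not increase false claims of non-inferiority.
- *That only 99 per arm would be randomised*, since the text says the calculation "revealed that 99 patients per intervention group need to be randomized". This is loose wording. The sentences that follow add 25 per group for dropout and arrive at 124.

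**Conclusion.** The point holds as a misprint in the sole statement of the primary test's significance level. The printed value is wrong by a factor of 100 and is incompatible with the stated sample size, which would have to rise from 99 to about 234–237 evaluable per arm to match it. The sample size itself is sound for a one-sided 2.5 %, so the margin, test and patient numbers need no change. The conclusion uses the article's own SD, margin and power. Its one assumption is a true difference of 0, the value at which the stated 99 is reproduced with a one-sided 2.5 %. The correction should still be made, because a confirmatory threshold should be readable from the protocol and not have to be back-calculated.

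**What to change.** In Statistical methods, Sample size, replace the printed level with a one-sided alpha of 2.5 % (0.025). In Analysis of primary endpoint, state the same level for the one-sided t-test. An equivalent wording is that non-inferiority is concluded if the upper limit of the two-sided 95 % confidence interval for μRYGB − μSG lies below 9 percentage points. It would also help to state that the calculation assumes a true difference of 0, if that is confirmed. Any analysis plan should be checked to see that it carries 2.5 % and has not copied the misprint. The cost is one line in each section, with no effect on recruitment, conduct or analysis.
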